### Blinding

2.4

Because of the intervention method, it may not be feasible to effectively blind both the participants and professionals engaged in the project.

### Assessments

2.5

Patients will be screened and enrolled at the Consultation and Psychosomatic Psychiatry Center of the University Hospital of Cagliari (San Giovanni di Dio Civil Hospital) and will be assessed before the treatment (t0), immediately post-intervention (t1), and after 6 (t2) and after 12 (t3) months post-intervention. The researchers responsible for measuring the outcomes will be three, and they will not be involved in the intervention phase. The following socio-demographic variables will be collected for each participant: gender and age; marital status; educational background; past and current occupational status; past and current organic physical illnesses; past and current mental health diagnoses; medications in use.

#### Primary outcomes

2.5.1

The primary outcome assesses the feasibility of the study, focusing on acceptability, tolerability (dropout rate), level of side effects and satisfaction. Variables in terms of acceptability, tolerability and satisfaction level will be assessed using an *ad-hoc* data sheet. Acceptability is measured as the proportion of recruited patients among those deemed eligible, while tolerability is assessed as the proportion of patients completing the trial intervention among those included.

The Italian adaptation of the Simulator Sickness Questionnaire (SSQ) will be used to record side-effects. The SSQ is a 16-item self-report questionnaire assessing the frequency of potential side effects related to the use of VR technologies, such as nausea, dizziness, headaches, eye fatigue, etc. (39).

#### Secondary outcomes

2.5.2

The secondary outcomes related to the preliminary clinical trial efficacy encompass cognitive functions (including visuospatial abilities, attention, memory, verbal and semantic fluency, and executive function), and personal and social functioning (symptoms of anxiety and depression, quality of life, emotional awareness, social functioning, and regulation of biological rhythms).

##### Personal and social functioning

2.5.2.1

The following self-report questionnaires will be administered:

Short form health survey with 12 items (SF-12), investigating dimensions of wellbeing including perception of general health, mental health, emotional and social functioning, and work and social roles. The questionnaire is validated in Italian (40).Brief social rhythms scale (BSRS), assessing the level of regularity in sleep–wake and appetite biological rhythms, and social rhythms through 10 items. The questionnaire is validated in the Italian language (41).Generalized anxiety disorder–7 item (GAD-7), based on DSM IV diagnostic criteria for generalized anxiety disorder, investigating the presence and severity of 7 anxiety symptoms in the previous 2 weeks, such as nervousness, inability to stop worrying, excessive worry, restlessness, difficulty relaxing, irritability, fear that something terrible will happen. The questionnaire is validated in Italian (42).Patient health questionnaire-9 items (PHQ-9), a questionnaire based on DSM IV diagnostic criteria for Major Depressive Disorder, investigating the presence and severity of 9 depressive symptoms in the previous 2 weeks, such as depressed mood, anhedonia, sleep and appetite disturbances, low energy, difficulty concentrating, motor behavior disturbances, loss of self-esteem, suicidal ideation; the cut-off for minor depressive disorder is represented by scores ≥5, and for major depression by scores ≥10. The questionnaire is validated in Italian (43).

##### Cognitive functions

2.5.2.2

They will be evaluated by:

Addenbrooke’s cognitive examination (ACE-R), a brief cognitive test with an administration duration of approximately 15 min in intact subjects, evaluating five cognitive areas: attention/orientation, memory, verbal fluency, language, visuo-spatial abilities. The test, with a maximum score of 100 and a cut-off for mild cognitive impairment of 66, includes the Mini Mental State Examination (MMSE). The test is validated in Italian (44).Matrices test, assessing indicators of selective attention (45).Rey’s word test, in both versions, assessing long-term memory, semantic memory, and specifying the phase of the mnemonic process in which the deficit occurs (46).Trail making test (TMT), in both versions, assessing cognitive functions such as cognitive flexibility, inhibitory control, and attention (47).Digit span normal and reverse, in both versions, assessing verbal short-term memory and working memory, respectively (48, 49).Stroop test, assessing selective attention, inhibition of irrelevant information, and cognitive flexibility (50).Frontal assessment battery (FAB), screening battery for global executive function through a series of cognitive and behavioral tests (51).Cognitive estimation test (CET), in both versions, assessing the ability for estimation and abstraction (52).Rey’s figure test, assessing praxis skills, visuo-spatial abilities, working memory, long-term memory, and executive functions (50).

### Intervention

2.6

The experimental group will participate in an immersive VR-based CR program utilizing the “CEREBRUM” software version 3.0.1 developed by “PRoMIND-Services for mental health Srls” in collaboration with “IDEGO-Virtual Psychology.” CEREBRUM is among the latest VR-implemented CR tools in psychiatric rehabilitation and was designed by clinicians and experts specializing in cognitive rehabilitation, is compatible with the hardware “Oculus Quest” VR viewer all-in-one headset, a CE-marked device developed by Meta Technologies.

The CEREBRUM app provides 52 exercises of varying difficulty divided by Memory and Learning, Cognitive Estimates, and Attention and Working Memory modules. During VR exposure, participants do not actively interact with the virtual environments themselves. Instead, the clinician guides the session by asking structured questions, following a manual, allowing the participant to engage with the scenario through their responses. This approach ensures that the exposure is not solely dependent on interaction with the virtual reality, but rather on the dialog facilitated by the clinician. The virtual scenarios offer a fully immersive exposure simulating everyday reality, including home and urban environments. The intervention includes 24 sessions over 3 months, with two sessions per week lasting 50 min each. Each session includes reception, psychoeducation and orientation to the tool, exercise psychoeducation, psychoeducation to the function targeted in the exercise, generalization phase, execution of the VR exercise with feedback (one of attention and working memory module), post-exercise comment, a second exercise (one of Memory and Learning or Cognitive Estimation modules) following the same structure (maximum VR exposure duration of 15–20 min), final comment, and homework. Some sessions could include a third exercise based on participant, session, and operator’s assessment. The generalization phase refers to the explanation of the function and its significance in the participants’ life context. For homework, practical suggestions are intended to be implemented by the patients in their daily life. A multidisciplinary team composed of one psychiatric rehabilitation technician and a speech language therapist will be involved in each session, emphasizing a comprehensive framework aligned with the healthcare needs of the participants. The selection of this intervention methodology, aiming to enhance the generalization of cognitive and personal functioning through a diversity of trained domains, aligns with the health needs of individuals with MCI. To ensure the generalization and standardization of the intervention, the operators involved are professionals working in rehabilitation. They undergo specific training for the tool and follow a precise intervention manual during the session. The only variations during the session occur in the psychoeducation and generalization phases, where personal examples from the participant are used.

### Control

2.7

The control group will include participants enrolled from the San Giovanni di Dio Civil Hospital and will receive conventional treatment, including general pharmacological and non-pharmacological interventions dependent on the health conditions of participants aged from 65 with MCI.

### Data analyses

2.8

The statistical analysis will use SPSS software (version 21). Intra-rater and inter-rater reliability for the evaluation of the outcomes will be measured using Kappa statistics. Descriptive statistics for sociodemographic variables and the level of satisfaction of the experimental intervention, will be presented as frequencies (percentages) or mean ± standard deviation. To assess homogeneity between the experimental and control groups regarding “sex” and “age” distributions, chi-square tests and one-way ANOVA will be employed. A multivariate analysis, one for each considered outcome, will be conducted to compare means between the intervention and non-intervention groups over time (pre-and post-intervention), applying Bonferroni’s correction. The normality assumption of dependent variables will be assessed for sphericity, with Mauchly’s test use to verify the equality of variances among all combinations of related groups. Missing data will be considered incomplete and therefore excluded from the analysis.

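### Kappa, with its type unstated, is the only rater-reliability statistic named, yet the examiner-scored cognitive tests are numeric; in unweighted form it can make closely agreeing raters look unreliable

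*Protocol article*

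**What the plan says.** The reliability plan is one sentence in section 2.8 of the protocol article: "Intra-rater and inter-rater reliability for the evaluation of the outcomes will be measured using Kappa statistics". It gives no weighting, no categories and no list of the tests covered.

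Three other statements bear on it:

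- **Who rates.** Section 2.5 (Assessments): "The researchers responsible for measuring the outcomes will be three".
- **What they rate.** The examiner-administered outcomes are the cognitive tests of section 2.5.2.2. For the ACE-R the article gives a range and a threshold: "The test, with a maximum score of 100 and a cut-off for mild cognitive impairment of 66".
- **How the outcomes are analysed.** Section 2.8 plans a multivariate analysis for each outcome that "will be conducted to compare means between the intervention and non-intervention groups over time", so the plan itself treats the scores as numeric.

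The personal and social functioning measures are introduced by "The following self-report questionnaires will be administered", and for side effects "The SSQ is a 16-item self-report questionnaire". No rater scores these.

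**The concern.** Unweighted kappa is chance-corrected exact agreement on categories. It ignores the distance between two ratings: 71 against 72 on the ACE-R counts the same as 51 against 91. On a fine-grained score, two examiners who are nearly always within a point or two of each other will often fail to match exactly, and kappa will be low. An ICC on the same data would be high.

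What is at stake is the reported quality of the cognitive assessments. Three assessors share the battery, and a feasibility trial is a natural place to show that they score it interchangeably. A low unweighted kappa could wrongly suggest that they do not. It also gives no error in score points.

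**Working it through.** **The plan's own figure.** There is none. The article states no expected kappa, target or precision, so the check compares what kappa and the ICC report on the same ratings.

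**Inputs from the article.** 30 participants (section 2.9), 3 assessors (section 2.5), ACE-R scored up to 100 with a cut-off of 66 (section 2.5.2.2).

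**Assumptions, not in the article.** Mean 70; true between-subject SD 6, 8 or 10; independent rater-error SD 0.25 to 2 points; scores rounded to whole points.

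**Formulas.** With true SD σ and rater-error SD e:

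- kappa = (p_o − p_e) / (1 − p_e), where p_o is observed and p_e chance exact agreement
- p_e ≈ 1 / (2√π · √(σ² + e²)) for whole-point normal scores
- ICC ≈ σ² / (σ² + e² + 1/12), where 1/12 is the rounding variance

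**One case by hand (σ = 8, e = 1).** Two raters differ with SD √2 = 1.41 points, and after rounding they match exactly in about 27% of cases. Chance agreement is 1 / (2 × 1.772 × 8.06) = 0.035. So kappa = (0.27 − 0.035) / (1 − 0.035) = 0.24. The ICC is 64 / (64 + 1 + 0.083) = 0.98.

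**Simulation** (30 subjects, 3 raters, 1,000 runs per setting; exact agreement and both kappas for one pair of raters, ICC for all three; σ = 8):

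| Rater-error SD | Exact agreement | Unweighted kappa | Quadratic-weighted kappa | ICC |
|---|---|---|---|---|
| 0.25 | 0.72 | 0.70 | 1.00 | 0.998 |
| 0.5 | 0.49 | 0.46 | 0.99 | 0.995 |
| 1 | 0.27 | 0.23 | 0.98 | 0.982 |
| 1.5 | 0.18 | 0.15 | 0.96 | 0.962 |
| 2 | 0.14 | 0.11 | 0.93 | 0.936 |

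The hand result of 0.24 against the simulated 0.23 reflects the small sample of 30.

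**Sensitivity.**

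- *True SD 6 to 10.* Kappa is 0.23 to 0.24 at error SD 1 (ICC 0.97 to 0.99) and 0.10 to 0.11 at error SD 2 (ICC 0.89 to 0.96).
- *Three-rater (Fleiss) kappa.* It stays within about 0.01 of the two-rater value.
- *Shorter 0–18 scale, assumed SD 3, error SD 0.5.* Kappa is 0.45 and ICC 0.96.
- *One rater always exactly one point higher (a single simulated sample).* Kappa is −0.03 and ICC 0.99.
- *ACE-R split at 66, error SD 1.* Kappa averages 0.88, so kappa behaves well on a true category.

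**The case against.** The strongest reply is that the article says only kappa, without a type. It condenses a fuller protocol, and an analysis plan that is not shown may specify quadratic weights or categories. With quadratic weights the coefficient matches the ICC in every setting tried, and on the ACE-R cut-off kappa is sound. This stands, and it makes the result conditional. It does not remove the point. The article commits to one statistic, the unqualified name ordinarily means the unweighted coefficient, and on the generous reading the text must still say so.

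Four stronger readings are tempting, and the document does not support them:

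- *Kappa must collapse on any wide scale.* At a fixed rater error it does not. Error SD 1 gives 0.23 on the 0–100 score (SD 8) and 0.26 on a much wider scale (assumed SD 35). What matters is rater error relative to one score unit.
- *Timed tests would show even lower values.* The article describes the Trail Making Test only by function ("Trail making test (TMT), in both versions, assessing cognitive functions such as cognitive flexibility, inhibitory control, and attention") and does not say that any test is scored as a time.
- *Kappa would be applied to the self-report questionnaires.* The sentence concerns rater reliability, and its natural reading covers outcomes that a rater evaluates.
- *Measurement error needed for the confirmatory trial would be lost.* The Discussion ties later sample-size planning to recruitment and retention. The repeat ratings would still exist, and an ICC could be computed from them.

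**Conclusion.** The point holds in a limited form. For the examiner-scored numeric tests, kappa in its ordinary unweighted form is a poor choice and can seriously understate agreement: about 0.2 against an ICC of about 0.98 at an error SD of 1 point, and about 0.1 against 0.94 at 2 points, with a true SD of 8.

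This rests on three assumptions: unweighted kappa, scores used in whole points, and rater differences of roughly half a point or more. The SDs are assumed, but the pattern is stable for true SDs from 6 to 10. If scoring is near-exact or the weights are quadratic, the problem largely disappears.

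The severity is minor. The reliability check is ancillary. A reader might infer that the efficacy comparisons or the primary feasibility results are compromised, but nothing in the article makes either depend on the reliability coefficient, and the sample of 30 is unaffected.

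**What to change.** Replace the sentence in section 2.8 with one that states:

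- for the examiner-scored numeric cognitive tests, intra- and inter-rater reliability is reported as an intraclass correlation (two-way random effects, absolute agreement, single rater) with 95% CI, together with the standard error of measurement in score points;
- plain kappa is used only for categorical ratings.

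If the investigators prefer to keep kappa for the numeric tests, specifying quadratic weights is an acceptable equivalent for the coefficient. The standard error of measurement should still be added.

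The cost is one sentence. The ICC uses the same repeat ratings that kappa would need, and the planned software provides it. The article says recruitment has not yet begun, so the change can be made before any data exist.

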### Randomization

2.3

Participants meeting the eligibility criteria will be randomly assigned to two groups (intervention and control group). A computer-generated randomization list will be used for the random allocation sequence, carried out at the University of Cagliari. A standard single blinding randomization procedure will be employed without stratification; however, if the sample will not be homogeneous, block stratification by age and sex, with a maximum of two blocks, will be implemented. An external statistician, not involved in the research project (thus not involved in assessments or interventions), will generate the two lists using a list generator and before it will anonymize the allocation using identification codes. The researchers involved in the assessments (initial and post-intervention) will be blinded to the participants’ group assignments.

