### Sample size considerations

2.9

In the registered clinical trial, our protocol outlined the recruitment and randomization of 30 eligible subjects in accordance with the predefined inclusion criteria.

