### Resource identification initiative

4.1

The primary objective of the trial is to comprehensively assess feasibility, particularly focusing on recruitment and retention rates. This evaluation provides essential insights for determining sample sizes in subsequent confirmatory trials. Additionally, to assess the side effect and satisfaction level of a VR-implemented CR tool, known as CEREBRUM. The secondary objective is to investigate cognitive and psychosocial variables. The hypothesis suggests that utilizing a CR with fully immersive VR program, with ecological instruments, can enhance cognitive abilities as well as other social and personal outcomes. The aim of this protocol study is to report the protocol of the trial, underlining methodological aspects in order to provide a response to the emerging health needs in line with the new evidences.

Indeed, the implementation of VR as a rehabilitative treatment in individuals with MCI is yielding positive results. Particularly, in a recent meta-analysis involving only people with MCI, a positive effect on clinical cognitive outcomes, specifically memory, language, and global cognition, was observed (29). However, few results are available regarding the improvement of clinical and functional outcomes due to the heterogeneity of variables and tools used, and the quality of the studies still need to improve (29, 53, 54). In general, the use of technological innovation and tools such as VR, based on the evidence described, can make the rehabilitation experience more engaging and facilitate the generalization of skills to real-life contexts, as the scenarios closely resemble those encountered in everyday life (54, 55). Naturally, technology should not replace the importance of the therapeutic relationship; rather, these are valuable tools that support rehabilitative techniques, with the relationship with the therapist remaining fundamental. Therefore, as in the intervention methodology used, exposure to VR is time-limited within each session.

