Finally, for the present trial the purposed methodology uses a technological innovation tools that can more easily transfer the trained skills into the real world while always considering an approach based on the therapeutic relationship (31). The methodological approach employed in the trial reflects a person-centered and recovery-oriented approach to rehabilitation (29, 35, 36, 56), enabling participants to improve their skills and achieve an overall enhancement in their health and psychological wellbeing. Moreover, it aligns with the new framework for developing complex interventions where ensuring the reproducibility of interventions is a crucial methodological consideration (34, 57). Despite the methodological strength of the methodology, the present study is designed primarily as a feasibility study. Subsequent studies intending to evaluate efficacy and cost-effectiveness will require with a larger sample size. The findings of the trial will be deliberated among all the authors.

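### Bonferroni-corrected tests on at least 13 secondary outcomes, with the correction family unstated, tell little at N = 30; baseline-adjusted estimates with 95% CIs would serve the feasibility aim better

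*Protocol article*

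**What the plan says.** All places are in the protocol article.

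- **Data analyses (2.8).** The efficacy analysis is "A multivariate analysis, one for each considered outcome", comparing means between the two groups "over time (pre-and post-intervention), applying Bonferroni’s correction". The section then invokes Mauchly's test. It states no alpha level and no family for the correction. This is the only efficacy analysis the article states.
- **Secondary outcomes (2.5.2).** Under Personal and social functioning, "The following self-report questionnaires will be administered" introduces four instruments: SF-12, BSRS, GAD-7 and PHQ-9. Cognitive functions lists nine: ACE-R, Matrices, Rey's word test, TMT, digit span, Stroop, FAB, CET and Rey's figure. Four of the nine are given in two versions, so the number of scores may exceed 13.
- **Sample size considerations (2.9).** The plan is "recruitment and randomization of 30 eligible subjects". The allocation ratio is not stated.
- **Purpose.** The abstract's Discussion says the trial is to supply data for a later confirmatory trial. Section 4.1 says "the present study is designed primarily as a feasibility study" and that studies of efficacy will need a larger sample.

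**The concern.** The plan commits the secondary outcomes to corrected significance tests in a trial that its authors describe as too small to evaluate efficacy. The wording allows two readings. If the correction runs across outcomes, each test has a very strict threshold. If it runs across comparisons within one outcome, the 13 or more outcomes are uncorrected against each other. Two analysts could both follow the section and reach different conclusions from the same data.

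At stake is what the next trial's planners take from this one. A useful moderate effect could be reported as absent for a given outcome, or a chance finding could be picked out as the promising one. Neither gives them what they need: the size of the difference and its uncertainty.

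**Working it through.** The article gives no power calculation, so there is no stated figure to reproduce.

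**Inputs from the article:** N = 30; two arms; 4 + 9 = 13 secondary instruments; one analysis per outcome; Bonferroni.

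**Assumptions:** 15 per arm (equal allocation, the split most favourable to power); two-sided alpha 0.05; standardised differences d of 0.5 and 0.8; baseline–follow-up correlation r = 0.7 where adjustment is shown, with other values noted. For the within-outcome reading, the family is taken as 3 or 6 comparisons; four time points (t0 to t3) give 4 × 3 / 2 = 6 pairs.

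**Step 1: power per outcome.** Two-sample t test, df = 28, noncentrality d × √(15/2): 1.369 at d = 0.5 and 2.191 at d = 0.8. The critical value is the t quantile at 1 − alpha/(2m) for a family of m. Baseline adjustment multiplies the variance by 1 − r² = 0.51, so d is divided by √0.51 = 0.714.

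| Family m | alpha/m | critical t | d = 0.5 | d = 0.8 | d = 0.5, r = 0.7 | d = 0.8, r = 0.7 |
|---|---|---|---|---|---|---|
| 1 (uncorrected) | 0.05 | 2.048 | 26% | 56% | 46% | 84% |
| 3 (within outcome) | 0.0167 | 2.546 | 14% | 38% | 28% | 70% |
| 6 (within outcome) | 0.0083 | 2.839 | 9% | 28% | 20% | 59% |
| 13 (across instruments) | 0.00385 | 3.152 | 5% | 20% | 13% | 48% |

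For m = 13, ANCOVA gives 8% and 29% at r = 0.5, and 22% and 69% at r = 0.8.

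**Step 2: effect detectable with 80% power.** For m = 13 it is 1.47 SD unadjusted and 1.47 × 0.714 = 1.05 SD at r = 0.7. Uncorrected and unadjusted it is 1.06 SD. With an assumed 20% loss (12 per arm) and m = 13 it is 1.69 SD unadjusted.

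**Step 3: error across outcomes on the within-outcome reading.** With each outcome held at 0.05 and 13 independent outcomes, 1 − 0.95¹³ = 0.487, about 49%. Positive correlation between outcomes would lower this.

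**Step 4: what estimation would give.** The 95% CI half-width in SD units is 2.048 × √(2/15) = 2.048 × 0.365 = 0.75 unadjusted, and 0.748 × 0.714 = 0.53 at r = 0.7. At 12 per arm it is 0.85 unadjusted. A Bonferroni interval for m = 13 would have half-width 3.152 × 0.365 = 1.15.

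**The case against.** **A reader might infer that the trial will look negative whatever the treatment does.** The documents do not support that. Even with the correction across all 13, unadjusted power per outcome is 36% at d = 1.0 and 82% at d = 1.5. If all 13 outcomes shared the effect, the simulated chance of at least one significant result, for between-outcome correlations from 0.5 to 0, is 31–51% at d = 0.5 and 68–94% at d = 0.8. Low power per test is not a near-certain negative trial.

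**The across-outcome reading is only one reading.** The sentence describes one repeated-measures analysis per outcome, so a correction within each outcome is at least as natural. This stands, and the 5% and 20% figures are therefore conditional. It does not rescue the plan, because that reading leaves the outcomes uncorrected against each other.

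**Bonferroni is not the main cause.** This also stands: at d = 0.5, uncorrected and unadjusted power is 26%. Loosening the correction would not make the tests informative for moderate effects. That argues for moving from testing to estimation.

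**The efficacy outcomes are secondary and preliminary, and the authors concede the limit.** This keeps the point modest. It also makes significance tests a poor choice for the one efficacy analysis that is stated.

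**The sample-size remark in section 4.1 does not concern these outcomes.** Its subject is the feasibility assessment, chiefly recruitment and retention, which "provides essential insights for determining sample sizes in subsequent confirmatory trials". The point therefore rests on the more general aim in the abstract's Discussion.

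**An article may leave intervals and the correction family to a fuller document.** True, and nothing in the section excludes reporting intervals. Their absence is not the finding. The finding is that the section fixes corrected tests as the analysis and words the correction so that it can be applied in two materially different ways.

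**Conclusion.** The point holds as a modest, low-cost improvement. Across 13 instruments, power per outcome at d = 0.5 to 0.8 is about 5–20% unadjusted and 13–48% with baseline adjustment at r = 0.7. Within each outcome (3 to 6 comparisons) it is 9–38% unadjusted, with up to about a 49% chance of a false positive somewhere among the outcomes. A non-significant result for a moderate effect would say little about the treatment, and a lone significant one could well be chance.

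These figures rest on equal allocation, alpha 0.05, no dropout and the assumed effects and correlations. Strong baseline correlation softens them appreciably at d = 0.8; dropout worsens them. They do not show that a beneficial treatment would almost surely be reported as ineffective.

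**What to change.** In Data analyses, replace the Bonferroni-corrected tests of the secondary outcomes with wording such as:

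> *Each secondary outcome is reported as a baseline-adjusted between-group difference with its 95% confidence interval. These analyses are exploratory; no claim of efficacy is based on statistical significance, and no multiplicity correction is applied.*

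If the tests are kept, state the family that the correction covers and the alpha level, and make the estimates and intervals the main secondary result.

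Two additions are optional and the sponsor's choice: naming one outcome in advance as the lead for planning, and sizing the next trial on a cautious upper limit for the SD rather than on the observed SD.

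**Cost.** No new data are needed. The analysis model and reporting change, and the trial gives up any efficacy statement based on p-values. The intervals will still be wide (half-width about 0.75 SD unadjusted, 0.53 SD at r = 0.7), so estimation does not enable the trial to show efficacy. The Trial status section says recruitment is about to begin, so the change could be made before any outcome data exist.

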### Study design

2.1

This study is a feasibility randomized controlled (two-arm) clinical study protocol, adhering to the CONSORT flow diagram extension for feasibility study (37). The protocol is written according to the SPIRIT Standard Protocol Items (38). The RCT will involve individuals aged 65 and above with MCI. The experimental group will participate in a three-month CR program utilizing fully immersive VR, consisting of two sessions per week in addition to standard care. In contrast, the control group will receive only standard care. Consistent with the study outcomes (primary outcome of feasibility and secondary outcome of preliminary efficacy measurement), a randomized controlled design is essential even at the feasibility stage to ensure greater scientific rigor. For both outcomes, the variables will be assessed through comparison between the two groups.

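### The only outcome analysis stated that could apply to the SSQ, a primary side-effect measure, is a tested comparison of means, which does not estimate how often VR users have side effects

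*Protocol article*

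**What the plan says.** - **Role of the SSQ.** Section 2.5.1 (Primary outcomes) makes side effects part of the primary outcome and describes the SSQ as "assessing the frequency of potential side effects related to the use of VR technologies". Section 4.1 states the aim as "to assess the side effect and satisfaction level of a VR-implemented CR tool, known as CEREBRUM".
- **Comparison.** Section 2.1 (Study design), having named feasibility as primary and preliminary efficacy as secondary, says: "For both outcomes, the variables will be assessed through comparison between the two groups". On the comparator it says: "In contrast, the control group will receive only standard care".
- **Analysis.** Section 2.8 (Data analyses) states one analysis of outcomes: "A multivariate analysis, one for each considered outcome, will be conducted to compare means between the intervention and non-intervention groups over time". The sentence limits this to the pre and post assessments and adds a Bonferroni correction. The number of tests in the Bonferroni family is not given.
- **Descriptive reporting.** Frequencies and percentages, or means and SDs, are assigned in 2.8 to "Descriptive statistics for sociodemographic variables and the level of satisfaction of the experimental intervention". Side effects are not on that list.
- **Missing data.** "Missing data will be considered incomplete and therefore excluded from the analysis".
- **Tolerability.** In 2.5.1, "tolerability is assessed as the proportion of patients completing the trial intervention among those included".

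**The concern.** The aim is a property of the VR tool: how often it makes people unwell, and how badly. A difference in mean SSQ between arms answers another question. It averages over users with and without symptoms, and its p-value gives no share affected.

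Two stated features add to the mismatch. First, section 4.1 pairs side effects with satisfaction, but 2.8 gives descriptive reporting to satisfaction only. Second, the exclusion rule could act on the people who matter most. A participant who stops because of nausea or dizziness, and so has no post-intervention SSQ, drops out of the comparison of means. The completion proportion counts that person as a non-completer but does not record why.

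The trial is meant to inform a confirmatory trial. Its planners need the proportion of VR users affected and how uncertain that proportion is.

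**Working it through.** **Inputs.** 30 randomised in total (2.9). Two arms with no ratio stated (2.3), so 15 per arm is an assumption. No VR in controls (2.1). The documents give no SSQ distribution, no expected side-effect rate and no Bonferroni family; values for these below are assumptions. The plan states no figure for side effects that could be reproduced.

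**Step 1: which stated analysis can apply to the SSQ.** Section 2.8 assigns Kappa to rater reliability, chi-square and ANOVA to balance in sex and age, and descriptive statistics to sociodemographic variables and satisfaction. Only the comparison of means is left. With two time points, the group-by-time test is equivalent to a t test on change scores.

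**Step 2: limiting case without noise.** Let k of n VR users share an equal, very large rise d, and let nobody else change.
- Difference in means: kd/n.
- Variance in the VR arm: d²·k(n−k)/[n(n−1)]. Variance in controls: 0.
- Hence t = √[(n−1)k/(n−k)] on 2n−2 df, and d cancels.

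For n = 15 (28 df, critical value 2.048):

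| k affected | t | p |
|---|---|---|
| 1 | √(14/14) = 1.00 | 0.33 |
| 2 | √(28/13) = 1.47 | 0.15 |
| 3 | √(42/12) = 1.87 | 0.07 |
| 4 | √(56/11) = 2.26 | 0.03 |

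**Step 3: simulation with noise.** 40,000 trials per scenario, unit-SD normal change scores, k VR users shifted by 2 to 4 SD, t test. The table gives the share of trials that are significant with the VR mean higher.

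| Scenario | k=1 | k=2 | k=3 |
|---|---|---|---|
| 15/15, alpha 0.05 | 4-5% | 7-9% | 11-19% |
| 15/15, alpha 0.05/2 | about 2% | about 4% | 6-9% |
| 15/15, alpha 0.05/4 | about 1% | about 2% | 3-4% |
| 12 VR/18 control, 0.05 | 5-6% | 10-16% | 17-35% |
| 18 VR/12 control, 0.05 | 3-4% | 5-6% | 8-10% |
| One affected user excluded (14 vs 15), 0.05 | 2-3% | 4-5% | 8-10% |

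**Step 4: the opposite pattern.** If all 15 VR users shift by 0.5 SD, detection at 0.05 is 26%; by 1 SD, 76%. A mean therefore suits a broad rise, and the low figures in step 3 depend on effects falling on a few users.

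**Step 5: would testing counts help?** No. Fisher's exact test for 3/15 against 0/15 gives two-sided p = 2 × C(15,3)/C(30,3) = 2 × 455/4060 = 0.22.

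**Step 6: what an estimate gives.** Exact (Clopper-Pearson) 95% intervals: 1/15 = 7% (0.2-32%); 2/15 = 13% (2-41%); 3/15 = 20% (4-48%). For 0/15 the upper limit is 1 − 0.025^(1/15) = 22%.

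**The case against.** The strongest reply is that the SSQ is never assigned to the comparison of means. Section 2.8 does not name it, and the sentence cannot be read literally for the rest of the primary outcome. Acceptability is settled before randomisation, tolerability is a proportion with no pre and post mean, and satisfaction concerns the VR intervention and is described. The sentence fits the scored secondary scales more naturally, and the wording about frequency in 2.5.1 might point to descriptive use of the SSQ. A fuller plan may contain harms tables. This stands in part: the link to the SSQ is an inference. But section 2.1 applies the between-group comparison to both classes of outcome, and 2.8 leaves no other rule that the SSQ could follow. The point therefore concerns a stated rule that fits badly, and does not rest on a missing harms table.

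A reader might infer more: that the plan will miss side effects, or will take a non-significant SSQ difference as evidence of safety. The documents do not support that. They contain no decision rule for side effects and no SSQ distribution. The low detection in step 3 reflects 30 participants and an assumed pattern, and testing counts does no better.

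Two further replies hold. The loss of a participant who stops is conditional, since 2.5.1 gives no SSQ timing and that person may still complete one. And controls without VR are useful: nausea, headache and eye fatigue also occur without VR, so a count in the VR arm alone cannot separate background symptoms.

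**Conclusion.** The point holds in a limited form. Followed as written, sections 2.1 and 2.8 put a primary side-effect measure under a Bonferroni-corrected test of means that does not estimate what 2.5.1 and 4.1 ask for, and that can leave out users who stop because of side effects. At about 15 per arm a non-significant result would be uninformative, chiefly because the sample is small. If effects fell on 1 to 3 users, detection would be 4-19% before any correction; if all users rose by 1 SD, it would be 76%. These figures assume 1:1 allocation, the stated shifts and an SSQ taken before and after in both arms. The case for change rests on the mismatch between the test and the question, which holds whatever the pattern. It is a cheap improvement; nothing here invalidates the design.

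**What to change.** In 2.8, add two or three sentences:

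1. The SSQ is exempt from the Bonferroni correction, and the side-effect conclusion does not rest on a significance test.
2. The main summary is the number and percentage of VR-exposed participants with a new or worsened symptom at or above a severity level fixed before data are seen, with an exact 95% CI.
3. A participant who stops because of side effects counts as affected, even without a post-intervention SSQ.
4. SSQ scores are shown descriptively for both arms, so that background symptoms and a broad mild rise are visible.

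The cost is small: SSQ data already planned, plus the reason for stopping. The severity level must be chosen in advance; section 2.10 says recruitment had not yet begun, so on that account there was time. The interval will be wide at about 15 VR users. The change improves estimation and reporting, and does not raise power.
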